### 1.2 General principles

Analysis and reporting of results will follow the CONSORT guidelines.[1] Baseline characteristics will be tabulated by intervention group (JEVaDA) and comparator group (HealthDirect JE fact sheet) using appropriate summary statistics. Data will be derived from those patients who meet inclusion criteria (currently living in Australia, aged 18 years or older, able to read and understand English and intend to travel to a country outside of Australia where JE is a risk within the next 6 months) and enrol in the study.

### 1.3 Study population

The intention-to-treat (ITT) population will consist of all participants who were randomised to receive either the intervention or comparator, regardless of whether they reviewed their allocated intervention or completed the pre- and post-surveys. The only exclusion will be participants who withdraw their consent by exiting the pre-intervention survey prior to the material allocation stage.

The modified ITT population will consist of all participants who were randomised and provided both pre- and post-intervention data for the primary outcome.

Analyses for the primary and secondary outcomes will be conducted in the ITT and modified ITT populations, with the modified ITT analysis considered the principal analysis.

## Section 2: Statistical analysis

### 2.1 Confidence intervals and p-values

For all statistical tests, a significance level of 5% will be employed (p value 0.05) and 95% confidence intervals will be reported.

### 2.2 Missing data

All available data will be used for the analysis. Multiple imputation will be used to handle any missing data.

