### **Vaccine uptake**

For participants who consent to the follow-up survey, uptake of JE vaccine will be assessed through self-reported responses to the question, "Did you receive a vaccine for Japanese encephalitis before your trip?". While this approach relies on self-reported data rather than clinical records, it is a pragmatic choice given the research team's capacity and the limitations of the Australian Immunisation Register, which does not require mandatory reporting of non-National Immunisation Program vaccines for adults. Additionally, it minimises participant burden and preserves anonymity.

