| I am clear about which is more important to me (the benefits or the risks and side effects) |                |       |                            |          |                   |
| I have enough support from others to make a choice                                          |                |       |                            |          |                   |
| I am choosing without pressure from others                                                  |                |       |                            |          |                   |
| I have enough advice to make a choice                                                       |                |       |                            |          |                   |

|                                           |  |  |  |  |  |
|-------------------------------------------|--|--|--|--|--|
| I am clear about the best choice for me   |  |  |  |  |  |
| I feel sure about what to choose          |  |  |  |  |  |
| This decision is easy for me to make      |  |  |  |  |  |
| I feel I have made an informed choice     |  |  |  |  |  |
| My decision shows what is important to me |  |  |  |  |  |
| I expect to stick with my decision        |  |  |  |  |  |
| I am satisfied with my decision           |  |  |  |  |  |

966

967

1009 [Questionnaire](#)

---

1010

1011 In late 2024, you were planning a trip to a JE endemic area in [pipe previous answer]. Did you take  
1012 your trip as planned?

1013 - Yes – skip to ‘please select the country you spent the most time in from the drop-down list’

1014 - No

1015 How did your plans change?

1016 - Cancelled the trip

1017 - Chose a different destination

1018 - Delayed the trip

1019 - Other (please specify)

1020 Please provide any further details about why your travel plans changed (optional). *Free text box.* –

1021 **end survey**

1022 Please review this list of countries before answering the next question:

1023 ☐ Bangladesh

1024 ☐ Bhutan

1025 ☐ Brunei Darussalem

1026 ☐ Burma (Myanmar)

1027 ☐ Cambodia

1028 ☐ China

1029 ☐ India

1030 ☐ Indonesia

1031 ☐ Japan

1032 ☐ Lao People’s Democratic Republic

1033 ☐ Malaysia

1034 ☐ Nepal

1035 ☐ North Korea

1036 ☐ Pakistan

1037 ☐ Papua New Guinea

1038 ☐ Philippines

1039 ☐ Russia

1040 ☐ Singapore

1041 ☐ South Korea

1042 ☐ Sri Lanka

1043 ☐ Taiwan

1044 ☐ Thailand

1045 ☐ Timor-Leste

1046 ☐ Vietnam

1047

1048 Since November 2024, have you travelled to any of the countries listed above?

1049 ☐ Yes

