1050 ☐ No – End survey

1051

1052 Please select the country you spent the most time in from the drop-down list (required)

1053 NB: drop-down menu limited to JE-endemic areas excluding Australia  
1054

1055 Did you visit a healthcare provider to discuss your trip before travelling overseas?

1056 - Yes

1057 - No – skip to 'Did you take any measures to avoid mosquito bites'

1058 Did you receive a vaccine for Japanese encephalitis before your trip?

1059 - Yes, I received the JEspect (inactivated) vaccine

1060 - Yes, I received the Imojev (live-attenuated) vaccine

1061 - Yes, but I don't recall which JE vaccine I received

1062 - No, I did not get vaccinated – skip to 'Why did you decide not to get vaccinated'

1063 - I don't remember

1064 How many vaccine doses did you receive?

1065 - 1 dose

1066 - 2 doses (28 days apart)

1067 - 2 doses (7 days apart)

1068 - I don't remember

1069 Why did you decide to get vaccinated? (Select all that apply)

1070 - I was worried about my risk of catching JE

1071 - I was worried about the lack of treatment options for JE

1072 - I wanted to do everything I could to reduce my risk of JE

1073 - My doctor recommended that I receive the vaccine

1074 - I wasn't sure if I could avoid mosquito bites at all times

1075 - I trusted that the JE vaccine is safe

1076 - I believed that the JE vaccine would protect me

1077 - The cost of the vaccine was not a concern for me

1078 - Other, please specify

1079 Why did you decide not to get vaccinated (Select all that apply)

1080 - I wasn't worried about my risk of catching JE

1081 - The lack of treatment options didn't worry me

1082 - I didn't think the risk of JE was high enough

1083 - My doctor did not recommend the vaccine

1084 - My doctor told me I did not need the vaccine

1085 - I was confident I could avoid mosquito bites

1086 - I was worried about possible side effects

1087 - I was not sure that the vaccine would protect me

1088 - I was not able to pay the cost of the vaccine

1089 - Other, please specify

1090 Did you take any measures to avoid mosquito bites while overseas?

1091 - Yes

1092 - No

- 1093        -    Can't recall
- 1094    **If yes,** what measures did you take? (matrix-style question. Response options: frequently,  
1095 sometimes, often)
- 1096        -    Wore long-sleeved shirts and long pants outdoors
- 1097        -    Applied insect repellent (e.g. containing DEET, picaridin or OLE) to exposed skin

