## 2.7 Secondary outcomes

Secondary outcomes and planned statistical analyses are summarised in Table 3.

**Table 3.** Secondary outcomes: summary of statistical analyses to be performed

| Analysis               | Outcome                                                                       | Groups compared             | Adjusted factors*                                   | Test                |
|------------------------|-------------------------------------------------------------------------------|-----------------------------|-----------------------------------------------------|---------------------|
| Knowledge of JE        | Number of post-intervention correct responses to nine JE knowledge statements | Intervention vs. comparator | Pre-intervention knowledge score, age, sex          | Poisson regression  |
| Intention to vaccinate | Change in participants intention to get vaccinated                            | Intervention vs. comparator | Pre-intervention intent to get vaccinated, age, sex | Logistic regression |
| Uptake of JE vaccine   | Self-reported pre-travel JE vaccine uptake                                    | Intervention vs. comparator | Post-intervention intention to vaccinate, age, sex  | Logistic regression |

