### **Secondary Outcome 3: JE vaccine uptake**

*Null hypothesis:* The online JE vaccine decision aid (JEVaDA) does not lead to a greater increase in pre-travel JE vaccine uptake compared to standard online health information (HealthDirect fact sheet) among Australian adults planning overseas travel to JE risk areas.

*Research question:* Does use of JEVaDA lead to a greater increase in pre-travel JE vaccine uptake compared to standard online health information (HealthDirect fact sheet) among Australian adults planning overseas travel to JE risk areas?

JE vaccine uptake will be measured through self-reported responses to the question, "Did you receive a vaccine for Japanese encephalitis before your trip?" in an optional follow-up survey. Responses will be coded as 1 for “Yes” and 0 for “No” or “I don’t remember”.

This outcome will be analysed using multivariable logistic regression. The dependent variable will be self-reported JE vaccine uptake (binary) and the primary independent variable will be group allocation. As intention has been shown to be strongly associated with actual uptake and may confound the relationship between intervention and uptake, post-intervention intention to vaccinate will be included as a covariate, alongside age and sex. Findings will be reported as adjusted odds ratios (aORs) with 95% CIs and p-values (Table 7).

**Table 7.** Logistic regression analysis of JE vaccine uptake

| Variable                                 | Adjusted odds ratio (aOR) | 95% CI | p-value |
|------------------------------------------|---------------------------|--------|---------|
| Intervention group
(reference=JEVaDA) |                           |        |         |
| Post-intervention intention              |                           |        |         |

|              |  |  |  |
|--------------|--|--|--|
| to vaccinate |  |  |  |
| Age          |  |  |  |
| Female sex   |  |  |  |

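### Applied as written to vaccine uptake, the SAP's impute-anything rule fills in an undefined outcome for people who took no trip and gives travellers without a provider visit the uptake of those who had one

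*Combined protocol and SAP*

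**What the plan says.** Three parts of the plan bear on uptake.

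- **Missing data.** SAP 2.2 states "Multiple imputation will be used to handle any missing data". It makes no exception by outcome or by reason, and names no imputation model or missing-at-random assumption.
- **Analysis sets.** SAP 1.3 states "Analyses for the primary and secondary outcomes will be conducted in the ITT and modified ITT populations", with modified ITT principal. Membership of that set requires that a participant "provided both pre- and post-intervention data for the primary outcome"; follow-up and travel play no part.
- **Outcome.** Protocol 5.7.2 is narrower: "For participants who consent to the follow-up survey, uptake of JE vaccine will be assessed through self-reported responses". SAP Secondary Outcome 3 also takes uptake from the optional follow-up survey and gives this coding: "Responses will be coded as 1 for “Yes” and 0 for “No” or “I don’t remember". It has no code for people who did not travel, were not asked or did not respond. The model adjusts for "Post-intervention intention to vaccinate, age, sex" (SAP 2.7, Table 3).

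The follow-up survey in Appendix 4 filters people before the uptake question. Anyone whose trip was cancelled, delayed, redirected or otherwise changed gets the item "Please provide any further details about why your travel plans changed (optional" and the survey then ends. A respondent with no travel to a listed country also exits. A traveller who saw no healthcare provider is routed past the question: "No – skip to 'Did you take any measures to avoid mosquito bites".

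**The concern.** The blanks in the uptake variable are of different kinds, and the SAP has one rule for all of them.

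- **No trip.** Vaccination before a trip that did not happen has no true value, so there is nothing to impute.
- **Travelled, no provider visit.** Being asked coincides exactly with having seen a provider. Every observed answer comes from an attender, so the data say nothing about non-attenders, and a better imputation model cannot repair that.
- **Opted out, did not respond, or delayed or redirected but still reached a risk country.** A true value exists and is unobserved. This is ordinary non-response.

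The second group matters for the comparison between arms. Protocol 4.1 says that the decision aid prompts users to consult a healthcare provider. If it works partly by raising attendance, the routing depends on arm, and an analysis that sees only attenders cannot detect that part of the effect. Uptake is one of the hypothesised benefits in protocol 3.1.

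**Working it through.** **Figures in the plan.** SAP 2.5 gives 350 completers and 500 recruited. With SD factor √(1 − 0.5²) = 0.866, n per group = 2 × [0.866 × (1.960 + 1.282) / 0.30]² = 175.1, which agrees with about 175; and 350 / 0.70 = 500. The documents give no rates for follow-up response, travel, provider visits or uptake. All such rates below are assumptions.

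**Step 1: share imputed.** Answered = 350 × response × travelled × provider visit. The ITT column assumes that only post-survey completers are followed up.

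| Response / travel / visit | Answered | Imputed, modified ITT (350) | Imputed, ITT (500) |
|---|---|---|---|
| 40 / 70 / 30% | 29 | 92% | 94% |
| 60 / 80 / 50% | 84 | 76% | 83% |
| 80 / 90 / 70% | 176 | 50% | 65% |

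In the middle row the 266 blanks are 350 × 0.4 = 140 non-responders, 210 × 0.2 = 42 responders with no trip, and 168 × 0.5 = 84 travellers with no provider visit. So 126 of 266 arise from the routing and not from non-response.

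**Step 2: what imputation puts there.** Assume 30% uptake among those asked, and none among people with no visit or no trip. Logistic imputation on the SAP's uptake covariates (20 imputations, 300 replicates) marks about 13 of the 42 no-trip responders and 26 of the 84 no-visit travellers as vaccinated. Over the set of 350, uptake set by the assumptions is 0.8 × 0.5 × 0.3 = 12%; after imputation it is about 31%.

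**Step 3: effect on the odds ratio.** Simulations with 350 participants, random missingness and 50 imputations from the model's own covariates (100 replicates each) gave these mean log odds ratios (SE):

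| Observed | Observed only | After imputation |
|---|---|---|
| 84 | 0.502 (0.525) | 0.508 (0.526) |
| 113 | 0.484 (0.442) | 0.481 (0.442) |
| 176 | 0.432 (0.351) | 0.426 (0.352) |

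Imputation of this kind adds almost no information and returns the observed-only answer.

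**Step 4: an effect acting through attendance.** Assume provider visits of 60% with the decision aid and 40% with the fact sheet, and 30% uptake among attenders in both arms. Among travellers, uptake is 0.6 × 0.30 = 18% against 0.4 × 0.30 = 12%, so the log odds ratio is ln[(0.18/0.82) / (0.12/0.88)] = 0.476. Simulation with skipped travellers coded as unvaccinated gives about 0.47. Among those asked, uptake is 30% in both arms, so the log odds ratio is 0 by construction; simulation gives about 0.02, whether observed-only or imputed. As a difference over the whole set, the expected value is 0.8 × 0.30 × (0.6 − 0.4) = 4.8 points; the simulated true mean was 4.5, and after imputation about −0.5.

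**The case against.** The best reply is that SAP 2.2 and 1.3 are general rules and the specific text should govern. Protocol 5.7.2 limits uptake to people who agree to follow-up, SAP Secondary Outcome 3 concerns pre-travel uptake from an optional survey, and a question that does not apply is not usually called missing. This shows that a narrower intent is plausible. But neither section exempts anyone from imputation or defines an uptake set, so the only written rule for a blank remains SAP 2.2.

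Other parts of the reply stand, and they rule out three stronger readings that a reader might infer.

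- **That every imputed value is invented.** This is not so for opt-outs, nor for delayed or redirected travellers who reached a risk country. For them, imputation under a stated missing-at-random assumption is legitimate. What is lacking is the stated model, a sensitivity analysis, and any knowledge of the opt-outs' travel status.
- **That a large imputed share by itself distorts the odds ratio or falsely narrows its interval.** Step 3 shows otherwise when imputation uses the model's own covariates. A richer model could behave differently, but the SAP specifies none.
- **That the trial would report inflated absolute uptake.** SAP Table 7 plans odds ratios only, so the 12% to 31% shift matters only if proportions are also reported.

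It is also fair to say that analysing only observed answers would be no cure. Step 4 shows that it keeps the same selection on provider visits.

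**Conclusion.** The point holds in a limited form. Read as written, the SAP imputes an outcome that is undefined for participants with no trip, and fills in travellers without a provider visit from attenders alone. The consequence is mainly one of meaning: an odds ratio that rests on follow-up respondents who travelled and saw a provider would carry an ITT or modified ITT label, and an arm effect acting through attendance would disappear (log odds ratio about 0.47 reduced to about 0.02 in the example).

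The imputed share of about 50-92% of modified ITT rests wholly on assumed rates. The loss in Step 4 rests on an assumed difference in attendance between arms and on non-attenders being unvaccinated; the documents establish neither. The matter concerns one secondary outcome. The primary analysis and its sample size are untouched. It should be corrected, because it changes what the trial can conclude about uptake.

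**What to change.** Amend SAP 1.3, 2.2 and Secondary Outcome 3, and reconcile them with protocol 5.7.2:

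1. Exempt uptake from the blanket rule in SAP 2.2.
2. Define the uptake set as follow-up respondents who travelled to a listed JE-risk country.
3. Treat no-trip respondents as not applicable and never impute them. As printed, the survey closes for everyone whose plans changed, and the later item on travel since November 2024 seems unreachable: one answer to the planned-trip item skips over it and the other leads to the end. Cancelled trips can be identified, but delayed, redirected or other changes should count as travel status unknown, that is, as non-response.
4. Keep travellers who skipped the question for lack of a provider visit in the set, coded as not vaccinated, with a sensitivity analysis that varies this coding. Some may have been vaccinated before; the pre-intervention survey allows for that answer.
5. Limit imputation to true non-response, with a stated model and assumption, labelled as sensitivity, and give best-case and worst-case bounds by arm.
6. Report counts by arm at each routing step.

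The text is short, but the change has costs. The denominator is smaller. The set conditions on travel, which happens after randomisation, and this must be stated as a limitation. SAP Section 3 describes Version 3 as final before analysis, so the change must be a dated amendment that says whether uptake data had been seen.

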### 2.3 Statistical software

All analyses will be conducted using StataBE 18.

### 2.4 Outcomes

The primary outcome will be post-intervention decisional conflict, as measured by the 16-item Decisional Conflict Scale (DCS)[2], with analyses adjusted for pre-intervention scores, age and sex. Secondary outcomes will include change in JE knowledge, change in intention to vaccinate and self-reported uptake of JE vaccine. Further details are included below.

## 2.5 Sample size analysis

Sample size estimates are based on detecting an effect size of 0.30 for the primary outcome, as recommended in the DCS User Manual [3]. Using the ANCOVA approach and assuming a modest correlation of 0.5 between pre and post-intervention DCS scores within-participant, we will have over 90% power (2-sided significance level of 0.05) to detect an effect size of 0.30 in the primary outcome with a sample size of approximately 175 participants per group (total 350 patients). Target recruitment was set at 500 participants to account for a 30% non-completion rate. The effect size is the difference in post-intervention DCS scores between intervention and comparator, adjusted for pre-intervention DCS score, and expressed as a fraction of the standard deviation of pre-intervention DCS scores.

## 2.6 Primary Outcome (Decisional conflict)

*Null hypothesis:* There is no difference in post-intervention decisional conflict between Australian adults using an online JE vaccine decision aid (JEVaDA) and those using standard online health information (HealthDirect fact sheet) when planning overseas travel to JE risk areas.

*Research question:* Does use of an online JE vaccine decision aid (JEVaDA) lead to a greater reduction in decisional conflict compared to standard online health information (HealthDirect fact sheet) among Australian adults planning overseas travel to JE risk areas?

The primary outcome is post-intervention decisional conflict, measured using the 16-item Decisional Conflict Scale. Each item is rated on a 5-point Likert (0=strongly agree to 4=strongly disagree). The total score is calculated by summing all item scores, dividing by the number of items, and converting to a 0-100 scale. Higher scores indicate greater decisional conflict and a need for additional support or information. Scores below 25 are associated with being able to implement a decision, whereas scores above 37.5 are associated with decision delay or feeling unsure about implementation.

Mean DCS scores (with 95% confidence intervals) will be reported by group at baseline (pre-intervention) and post-intervention. Individual-level changes in score will be depicted in a waterfall plot, showing the change from baseline by group, with groups represented in different colours.

The primary analysis will use linear regression with an analysis of covariate (ANCOVA) structure where the post-intervention score is the dependent variable, the intervention group is the independent variable, and the pre-intervention DCS score, age and sex are included as covariates. Results will be presented in table format (Table 1). The table will include the estimated coefficients for each predictor (intervention group, baseline DCS score, age, sex) along with their 95% confidence intervals and p-values.

**Table 1.** Results of primary ANCOVA model predicting post-review DCS scores

| Variable                              | Coefficient | 95% CI | p-value |
|---------------------------------------|-------------|--------|---------|
| Intervention group (reference=JEVaDA) |             |        |         |
| Baseline DCS                          |             |        |         |
| Age (continuous)                      |             |        |         |
| Female sex (vs. male)                 |             |        |         |
| Non-binary (vs. male)                 |             |        |         |

The DCS has five subscales. Subscale scores will be presented in a similar way to the Total DCS score and will be considered secondary outcomes (Table 2).

**Table 2.** Decisional conflict scale and subscales: summary of statistical analyses to be performed

| Analysis                    | Outcome                                                  | Groups compared             | Included covariates                                          | Test   |
|-----------------------------|----------------------------------------------------------|-----------------------------|--------------------------------------------------------------|--------|
| Decisional conflict         | Post-intervention DCS score                              | Intervention vs. comparator | Pre-intervention DCS score, age, sex                         | ANCOVA |
| Informed subscale           | Post-intervention informed subscale DCS scores           | Intervention vs. comparator | Pre-intervention informed subscale score, age, sex           | ANCOVA |
| Values subscale             | Post-intervention values subscale DCS scores             | Intervention vs. comparator | Pre-intervention values subscale score, age, sex             | ANCOVA |
| Support subscale            | Post-intervention support subscale DCS scores            | Intervention vs. comparator | Pre-intervention support subscale score, age, sex            | ANCOVA |
| Uncertainty subscale        | Post-intervention uncertainty subscale DCS scores        | Intervention vs. comparator | Pre-intervention uncertainty subscale score, age, sex        | ANCOVA |
| Effective decision subscale | Post-intervention effective decision subscale DCS scores | Intervention vs. comparator | Pre-intervention effective decision subscale score, age, sex | ANCOVA |

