## 5.2. RANDOMISATION

Individually stratified randomisation will be used to allocate participants to either the intervention or control group. This process will ensure that groups are balanced according to baseline demographic characteristics collected from the pre-intervention survey, including age group, gender and geographic location (state or territory of residence). We will utilise the automated randomisation module in REDCap, with access requested from the Monash Helix team. To maintain blinding, a statistician independent of the central research team will build and upload the randomisation tables to REDCap. Participants will be randomly assigned to their respective groups based on their survey responses. Upon completion of the pre-intervention survey, participants will be directed to the materials corresponding to their assigned group based on the randomisation outcome.

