## 5.10. DATA ANALYSIS

Data will be analysed using the statistical analysis software package STATA v18. Baseline characteristics of participants will be tabulated by randomization groups. Continuous variables will be summarised using means (standard deviations), while categorical variables will be summarised by frequencies (percentages). Graphical visualisations will be conducted where appropriate.

Linear regression will be used to estimate the effect of intervention (vs control) on change in DCS scores (post- vs. pre-intervention) with pre-intervention DCS scores adjusted for in the model, i.e. an analysis of covariance (ANCOVA) structure. Statistical significance will be declared if a two-sided p-value is <0.05.

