### About you

**This next set of questions asks about you**

Which State or Territory do you currently live in? (please select from the list)

*NB: a drop-down list will be provided*

What is your age (in years)? (drop-down list: 18-100)

What is your gender?

|                                                 |                          |
|-------------------------------------------------|--------------------------|
| Female                                          |  |
| Male                                            |  |
| Non-binary/gender diverse                       |  |
| My gender identity isn't listed. I identify as: | [text box]               |
| Prefer not to say                               |  |

In which country were you born? (please select from the list)

*NB: a drop-down list of all possible options will be provided, with Australia pinned at the top*

Which country or countries were your parents or guardians born? (select all that apply)

- ☐ Australia
- ☐ China
- ☐ India
- ☐ Malaysia
- ☐ Philippines
- ☐ New Zealand
- ☐ South Africa
- ☐ United Kingdom (England, Scotland, Wales, Northern Ireland)
- ☐ Vietnam

627 ☐ Other, please specify

628

629

630 Do you speak a language other than English at home?

|                             |                          |
|-----------------------------|--------------------------|
| No – English only           |  |
| Yes – Other, please specify | [text box]               |

631

632 Are you of Aboriginal or Torres Strait Islander origin?

|                             |                          |
|-----------------------------|--------------------------|
| No                          |  |
| Yes, Aboriginal             |  |
| Yes, Torres Strait Islander |  |

633 *For people of both Aboriginal and Torres Strait Islander origin, mark both 'Yes' boxes*

634

635 What is the highest educational qualification you have completed?

|                                                 |                          |
|-------------------------------------------------|--------------------------|
| Year 11 or below                                |  |
| Year 12 or equivalent                           |  |
| Certificate (e.g. TAFE or trade certificate)    |  |

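### State or territory is a stratification factor but appears in no planned model; in the linear models this costs a little precision and causes no bias

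*Combined protocol and SAP*

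**What the plan says.** Protocol 5.2: "Individually stratified randomisation will be used to allocate participants to either the intervention or control group". The groups are to be balanced on baseline characteristics "including age group, gender and geographic location (state or territory of residence"). The pre-intervention survey (Appendix 4, About you) collects state or territory before allocation.

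The planned models are:

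- **Protocol 5.10, primary outcome:** linear regression "with pre-intervention DCS scores adjusted for in the model", with no other covariate named.
- **SAP 2.6, primary outcome:** an ANCOVA in which "the pre-intervention DCS score, age and sex are included as covariates". Table 1 enters age as a continuous variable.
- **SAP Table 2, five DCS subscales:** the same pattern, for example "Pre-intervention informed subscale score, age, sex".
- **SAP Table 3, knowledge:** "Pre-intervention knowledge score, age, sex". The intention model uses baseline intention, and the uptake model uses post-intervention intention, each with age and sex.

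State or territory is in none of these. In the text supplied, the asterisk on the adjusted-factors column of Table 3 has no footnote, but the result shells in Tables 5 to 7 have no state row. Neither document explains the omission or plans a sensitivity analysis that includes the factor.

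**The concern.** Stratifying on state makes the arms more alike on state than simple randomisation would. A model without state computes its standard error as if that balance had arisen by chance. If state predicts the post-intervention DCS score, its variation stays in the residual. The reported standard error is then a little too large, the interval a little too wide and the test a little conservative.

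The SAP adjusts for counterparts of two of the three stratifiers and says nothing about the third, so a reader cannot tell a decision from an oversight.

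There is a smaller, related inconsistency. The survey has one gender item with five responses, and randomisation uses gender, but the SAP names the covariate sex. Table 1 has female and non-binary rows against male. Tables 5, 6 and 7 have a female row only. No table says how the two remaining survey responses (identity not listed, prefer not to say) are handled.

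**Working it through.** **1. The plan's own figure.** Inputs from SAP 2.5: effect size 0.30 SD, pre-post correlation 0.5, two-sided alpha 0.05, 175 per group, 30% non-completion.

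- Residual SD = sqrt(1 − 0.5²) = 0.866.
- n per group for 90% power = 2 × (1.960 + 1.282)² × 0.75 / 0.30² ≈ 175.1, rounded up to 176. Power at 175 per group is 89.98% (normal approximation).
- Recruitment = 350 / (1 − 0.30) = 500.

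The stated figures reproduce.

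**2. Effect of omitting state under exact balance.** Let R² be the share of residual DCS variance that state explains. The documents give no value, so a range is assumed. With exact balance on state:

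- the reported SE is too large by the factor 1/sqrt(1 − R²);
- the true type I error without state is 2 × [1 − Φ(1.96/sqrt(1 − R²))].

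| Assumed R² | SE too large by | Type I error, state omitted | Power, omitted | Power, included | n per group for 90% power, included |
|---|---|---|---|---|---|
| 0 | 0 | 0.050 | 90.0% | 90.0% | 176 |
| 1% | 0.5% | 0.049 | 90.1% | 90.3% | 174 |
| 2% | 1.0% | 0.048 | 90.2% | 90.6% | 172 |
| 5% | 2.6% | 0.044 | 90.6% | 91.4% | 167 |
| 10% | 5.4% | 0.039 | 91.1% | 92.7% | 158 |

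At R² = 3% the SE is too large by 1/sqrt(0.97) − 1 = 1.5%.

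**3. Effect after 30% loss.** The principal analysis set (SAP 1.3) keeps only participants with pre and post data, so balance among those analysed is not exact. This was simulated with 500 randomised and 30% lost at random. Assumptions not taken from the documents: eight jurisdictions with uneven shares, four age groups, two gender groups, blocks of 4, and 4,000 runs per null setting.

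- R² = 0: mean SE 0.0929 without state and 0.0934 with it, ratio 0.995. Adding a useless state factor costs about 0.5%.
- R² = 5%: 0.0929 / 0.0910 = 1.021.
- R² = 10%: 0.0928 / 0.0885 = 1.049.

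Applying the 0.995 cost to the exact-balance factors gives 0.995 × 1.005 ≈ 1.000 at R² = 1% and 0.995 × 1.015 ≈ 1.010 at R² = 3%. A separate simulation gave 0.999 and 1.010. The gain is therefore nil at 1% and about 1% at 3%.

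**4. Bias and type I error.** For a true effect of 0.30, the mean estimate without state lay between 0.297 and 0.303 in all settings. Simulated type I error without state was 0.045 (R² = 5%) and 0.039 (R² = 10%) with full retention of 350. With 30% loss it was 0.047 at both. Monte Carlo error is about sqrt(0.05 × 0.95 / 4000) = 0.003. There is no sign of inflation.

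**5. Degrees of freedom.** Table 1 implies six coefficients (intercept, group, baseline DCS, age, two gender terms), so 350 − 6 = 344 residual degrees of freedom. Seven terms for eight jurisdictions leave 337.

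**The case against.** The strongest reply is that the omission hardly matters. R² is assumed, and neither document shows that state predicts post-intervention DCS once baseline DCS is in the model. Both scores are planned for one web session (Protocol 5.3). After the planned loss, the gain at R² = 1% disappears. All of this stands, and it limits the point to a small improvement in precision. The protocol does mention JE detection in four Australian states in 2022, which makes some variation by state plausible but does not quantify it.

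A second reply is that the remedy can do harm. Uptake comes from an optional follow-up, and the protocol describes JE vaccine uptake among travellers as poor. Up to seven state terms could leave sparse cells or separation there. This stands too, so the fix should not be imposed on every model.

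A third reply is that the SAP already departs from strict design fidelity by using continuous age where the stratifier is age group, and that the gender point is mostly labelling. Table 1's non-binary row suggests that sex means the survey's gender item. Both are fair. They make these details secondary but do not explain why state is absent.

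A reader might infer more than the documents support:

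- **That the primary result is biased or its test invalid.** The calculations show no bias and, if anything, a slightly conservative test.
- **That the same standard-error argument covers every model.** It describes the linear ANCOVAs. In the logistic models, adding a prognostic factor changes the conditional odds ratio being estimated; leaving it out gives an odds ratio nearer 1. That is not simply a matter of shrinking the standard error.

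**Conclusion.** The mismatch is real and unexplained: state or territory is a named stratifier and is in none of the planned models. For the primary and subscale ANCOVAs the consequence is at most a slightly inflated standard error. It is about 0.5% to 1.5% for an assumed R² of 1% to 3% under exact balance, and roughly 0% to 1% after 30% random loss. Under exact balance, including state at R² = 1% to 2% would be worth two to four participants per group (176 against 174 or 172). The planned sample size need not change.

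These figures rest on the assumed R², on the assumed jurisdiction shares and block size, and on loss unrelated to arm or outcome. They do not extend to the knowledge, intention and uptake models. The gender inconsistency is a matter of coding and table shells. It should be settled, but the documents do not give the categories used in the randomisation tables, so no stronger claim can be made.

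**What to change.** - **Primary and subscale ANCOVAs:** add state or territory as a categorical covariate, with small jurisdictions pooled by a rule written down without reference to outcomes. SAP Section 3 describes Version 3 as final before data analysis. If analysis has begun, keep the planned model and report the state-adjusted one as a labelled sensitivity analysis.
- **Knowledge, intention and uptake models:** add the pooled factor only where numbers per category and events allow, with particular care for uptake. State that in the two logistic models the adjusted odds ratio is conditional on state and so differs from the one without it.
- **Gender:** define one coding for all models, including the two survey responses that no table covers, use one label for the variable, and make Tables 5 to 7 consistent with Table 1.

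The cost is SAP wording, up to seven of about 344 residual degrees of freedom in the ANCOVAs (fewer after pooling), and a risk of sparse cells in the uptake model. No new data are needed, because the survey already collects state or territory before allocation.
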